### Recruitment

#### Overview

A key goal of the study is to explore methods to collect a representative study sample that reflects the relative proportions of various demographic subgroups and their intersectionalities in adults of the US population. For example, according to the US Census Bureau [17], 51% of the population is female and 44% of adults are between 20 and 44 years of age. Among those who reported a single race, about 13% are African American, 6% are Asian, and 74% are White. A February 2021 Gallup poll [18] reported that 5.6% of US adults identified themselves as lesbian, gay, bisexual, or transgender; 86.7% said that they were heterosexual or straight; and 7.6% refused to answer. In the past, some subgroups have been traditionally underrepresented in health studies (eg, female individuals; African American individuals; and those with a lesbian, gay, bisexual, transgender, queer, intersex, and asexual orientation) [19], and recent reviews have emphasized the importance of setting explicit recruitment goals in overcoming these biases [19,20]. As such, a key aim of the study is to learn more about how to increase the participation of traditionally underrepresented groups in digital health studies.

To explore methods to overcome recruitment barriers of traditionally underrepresented subgroups and make sure the study sample reflects sufficient diversity, we will pursue a two-prong approach: (1) a primary-augmented 2-wave metered recruitment schema and (2) multistakeholder engagement. Metered recruitment schema refers to the potential delay of eligible study participants in consent and enrollment (baseline characterization and initiation into the monitoring portion of the study). The pace of enrollment will be adapted based on study and clinical bandwidths and the distributions of demographic characteristics, with metering instituted by invitation to consent. The research team plans to begin the metered recruitment strategy once the study has achieved or has nearly achieved the enrollment of 10,000 participants. Depending on the distribution of key demographic variables, once consent and appropriate permissions are obtained, enrollment and initiation of monitoring will commence. To help reduce the effect of seasonality and other external factors on the data collected in this study, we are careful to design the strategy to recruit participants in a balanced manner across time and outside of periods containing major seasonal holidays.

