#### Wave 2 (Augmented Enrollment)

Upon the completion of wave 1, wave-2 efforts will discontinue the enrollment of sufficiently represented groups and focus entirely on increasing the participation of underrepresented groups, as defined by race and ethnicity (eg, African American, Asian, Latina or Latino, Native Americans or Indigenous, and White populations), biological sex at birth (female and male), age (18-40 and over 40 years), sexual orientation or gender identity (heterosexual and lesbian, gay, bisexual, transgender, queer, intersex, and asexual), and whether participants are Fitbit users. Multistakeholder engagement refers to the study’s collaboration with major stakeholders such as active groups or key opinion leaders of underrepresented groups of interest to codevelop adaptive recruitment goals and strategies.

The study will aim to recruit a study sample that reflects enriched participation of traditionally underrepresented groups in the United States. The wave-2 targeted recruitment strategy will include 5 demographic factors in addition to the ownership of Fitbit devices. If wave-1 enrollment is not sufficiently at parity with population representation, wave-2 efforts will target up to an additional 4000 participants to demographically balance the aggregate sample (potential total n≤14,000).

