## Results

At the time of submission, the study infrastructure and app have been designed and built, the institutional review board of the University of Oregon has approved the study protocol, and data collection is underway. Data from 4182 enrolled participants have been collected as of March 27, 2023.

Table 1 shows the distribution of participants enrolled in the DWB study at the time of writing. We have been able to achieve a demographic split relatively similar to the 2021 US Census data [17] in terms of race, biological sex, age, and sexual orientation.

Figure 3 shows the geographic distribution of the participants based on home state. This map illustrated the geographic representation enabled by performing a study with our mobile platform and ubiquitous wearable and smartphone sensing.

**Table 1 table1:** Comparison between our study sample and the demographic breakdown of the US adult population. Statistics as of March 27, 2023.

Factor (level)		2021 US census [17], %		Digital Well-Being study, %

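### The two age benchmarks attributed to the same census source (44% of adults aged 20-44; 55% of adults aged 18-40) cannot plausibly both be right, so the claimed parity on age is unverified

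*Protocol article*

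**What the plan says.** Methods, Recruitment, Overview gives the population age structure as "44% of adults are between 20 and 44 years of age", introduced by "according to the US Census Bureau [17", that is, reference 17.

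Results, Table 1 compares the sample with the "demographic breakdown of the US adult population". Its benchmark column is headed "2021 US census [17", the same reference. The age rows read 55% (census) and 54% (study) for 18-40, and 45% and 46% for 40+. The sample size follows from "Data from 4182 enrolled participants have been collected as of March 27, 2023".

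From this table the Results section concludes that the split is "relatively similar to the 2021 US Census data [17] in terms of race, biological sex, age, and sexual orientation".

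Wave 2 (Augmented Enrollment) is to stop enrolling groups that are sufficiently represented and concentrate on those that are not. Age is one of its factors, in the bands "age (18-40 and over 40 years". Wave 2 may add up to 4000 participants to bring the combined sample into demographic balance, for a total of up to 14,000.

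**The concern.** The two census figures carry the same reference and the same stated base, and their age bands overlap almost entirely. A band that adds only ages 18 and 19 and drops ages 41 to 44 should hold a share close to, and probably below, 44%. Table 1 shows it 11 points higher.

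The study's 54% sits one point from Table 1's benchmark, and the statement of similarity on age rests on that. If the benchmark is wrong, the statement may be wrong too. Table 1 is also the only place where the article gives a population figure in wave 2's age bands, so an error there could carry over into the decision on which age band stays open. The aim most exposed is the eighth, a real-world baseline across a representative population. The description of use patterns by age in the first aim does not depend on the overall age mix.

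**Working it through.** **Inputs.** Share of adults aged 20-44: 44% (Recruitment, Overview). Share aged 18-40: 55% census, 54% study (Table 1). Sample: 4182 (Results). Wave sizes: 10,000 and up to 4000 (Wave 1 and Wave 2). The share aged 18-19 is not in the article and is treated as an assumption.

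**Can the 55% be reproduced from the 44%?**

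share(18-40) = share(18-19) + share(20-40), and share(20-40) ≤ share(20-44) = 44%.

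- Required share(18-19) ≥ 55 − 44 = 11% of adults, or 5.5% per year of age. The average in 20-44 is 44/25 = 1.76% per year, so the ratio is 5.5/1.76 = 3.1. This also needs nobody to be aged 41-44.
- With the most favourable rounding: 54.5 − 44.5 = 10%, or 5.0% per year against 44.5/25 = 1.78%, a ratio of 2.8.
- With an even spread over 20-44: share(20-40) = 21 × 1.76 = 36.96%, so 18-19 must hold 55 − 36.96 = 18.04%, about 5.1 times the average density.

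The 55% is not reproduced under any of these. The overlap of Table 1's bands at age 40 does not explain it: one year of age is worth about 1.8 points, against a gap of at least 10.

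**What the 44% implies for 18-40, if it is right**

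| Assumption | Share aged 18-40 | Study's 54% minus this |
|---|---|---|
| Even density, 18-40 = 23 years | 23 × 1.76 = 40.5% | +13.5 points |
| Nobody aged 41-44; 18-19 at average density | 44 + 2 × 1.76 = 47.5% | +6.5 points |
| Nobody aged 41-44; 18-19 at twice average density | 44 + 4 × 1.76 = 51.0% | +3.0 points |

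The 40.5% is an even-density value, not a floor. A linear tilt of ±30% across ages 20-44, with 18-19 given the density of age 20, moves it between about 37.6% and 43.4%. The direction is the same in every case. The standard error of 54% in 4182 people is √(0.54 × 0.46/4182) = 0.8 points, so sampling error is not the main uncertainty.

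**Illustration for wave 2.** Assume the interim mix holds to 10,000 (5400 aged 18-40), all 4000 places are used, and balancing is on age alone. The number aged 18-40 needed in wave 2 is 14,000 × p − 5400.

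| Benchmark p for 18-40 | Needed aged 18-40 | Over-40 share of wave 2 |
|---|---|---|
| 55% (Table 1) | 2300 | 1700/4000 = 42.5% |
| 51.0% | about 1740 | about 56% |
| 47.5% | 1250 | 69% |
| 40.5% | 270 | 93% |

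**The case against.** A reader might infer that over-40s are in fact under-represented. The article does not support that, because it does not show which figure is wrong. The 44% appears in an illustrative sentence; if that number or its base is the slip, Table 1 may be right and the sample at parity. This objection stands, and the shortfall can be stated only conditionally.

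A reader might also infer that Table 1 decides who stays open in wave 2. No section says so. Table 1 is an interim description at 4182 participants. The Wave 1 section has the investigators assess participation and revise the wave-2 targets when wave 1 ends, and the Wave 2 section adds adaptive goals set with stakeholders and balances on five demographic factors plus Fitbit ownership. The plan therefore has a point at which the error could be caught, although nothing says the benchmark would be re-derived there. The wave-2 counts are illustrations, not predictions.

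It is tempting to treat 47.5% as a firm ceiling. It is not, because it assumes a density for ages 18-19 that the article does not give; doubling that density gives 51%. A swap of the 55% and 45% rows is also conceivable, but it is conjecture: 45% lies above the even-density 40.5% and would need few adults aged 41-44.

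Finally, the abstract and Discussion concede that the demographic match is imperfect. Neither names age, and the Results claim similarity on age explicitly. None of these points removes the contradiction between the two stated figures.

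**Conclusion.** The contradiction holds. With the same cited source and the same stated base, the two figures could agree only if ages 18 and 19 held at least 10-11% of adults, about three times the yearly density of ages 20-44, and nobody were aged 41-44. At least one figure, or its base, is wrong.

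The consequence is conditional. If the 44% is right, the 18-40 group is over-represented by about 3 to 13.5 points on the assumptions shown, and over-40s are correspondingly short. If the 44% is wrong, the sample may be at parity and only that sentence needs changing. A misdirected wave 2 follows only if Table 1's benchmark is the one used to judge parity. No hypothesis test described in the article uses the benchmark. This should be fixed before wave 2, but it does not undermine the study's analysis plan.

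**What to change.** Before wave-2 targets are set:

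1. Recompute the adult age distribution from reference 17 in exactly the enrolment bands, and state where age 40 falls. Table 1's 18-40 and 40+ overlap, while the Wave 2 section uses over 40.
2. Correct whichever is wrong, the sentence in the recruitment overview or the age rows of Table 1, and state the base of each figure.
3. Use the corrected value to decide whether either age band counts as sufficiently represented.
4. Keep or withdraw age in the Results statement of similarity accordingly.

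The cost is one lookup, one corrected sentence or table row and, if the gap is confirmed, a revised wave-2 age target and a less favourable reported match on age.

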#### Wave 1 (Open Enrollment With Enriched Recruitment)

During the initial several weeks that the study is open, we anticipate enrollment of up to approximately 1000 new participants per week (but will not limit to this pace). Enrollment will increase as infrastructure allows. An increase in consecutive enrollment of up to 10,000 new participants who are eligible for study participation will be invited to begin the enrollment process. The study will monitor the progress in recruiting traditionally underrepresented groups. Recruitment efforts will focus on enriched representations, with recruitment via email, social media, and Fitbit in-app notifications. Posts will be made on social media platforms, leveraging the reach and audience of the University of Oregon and Google accounts. In-app notifications will be made in the Fitbit app, and these notifications ensure high visibility of the study. At the conclusion of wave 1, the study investigators will assess study participation rates and revise the enrollment targets for wave 2.

#### Wave 2 (Augmented Enrollment)

Upon the completion of wave 1, wave-2 efforts will discontinue the enrollment of sufficiently represented groups and focus entirely on increasing the participation of underrepresented groups, as defined by race and ethnicity (eg, African American, Asian, Latina or Latino, Native Americans or Indigenous, and White populations), biological sex at birth (female and male), age (18-40 and over 40 years), sexual orientation or gender identity (heterosexual and lesbian, gay, bisexual, transgender, queer, intersex, and asexual), and whether participants are Fitbit users. Multistakeholder engagement refers to the study’s collaboration with major stakeholders such as active groups or key opinion leaders of underrepresented groups of interest to codevelop adaptive recruitment goals and strategies.

The study will aim to recruit a study sample that reflects enriched participation of traditionally underrepresented groups in the United States. The wave-2 targeted recruitment strategy will include 5 demographic factors in addition to the ownership of Fitbit devices. If wave-1 enrollment is not sufficiently at parity with population representation, wave-2 efforts will target up to an additional 4000 participants to demographically balance the aggregate sample (potential total n≤14,000).

### Ethical Considerations

If they choose to enroll, participants will be directed to a consent form administered via an in-app onboarding flow that describes the data that are collected and how they are used to advance the goals of the study. Each prospective study participant must pass the eligibility survey before proceeding to an assurance of understanding flow, where they are given a summary of the summary and key points of the consent. They are then quizzed on this content before they can proceed. There are multiple points to ensure comprehension of the study and consent. Prospective study participants agree to an e-consent, which provides short explanations for the data they are sharing and how they are used and a long form consent, which is a full institutional review board–approved consent form detailing the data use and rights. In addition, at the top of the form is a textbox including basic details of the study designed to make sure participants receive the most critical details, regardless of how.

The consent form will be associated with a unique participant ID that is stored securely. The purpose of this ID is to be able to link the consent form to the data collected in order to confirm that data were collected with consent if needed. As mobile sensing is nonintrusive, participants may easily forget they are participating in the study; therefore, the participants will receive daily notifications reminding them that they are enrolled in the study.

Participants will be informed that if they choose to withdraw, and they will have the option to remove or retain all or part of their data. In addition, even if they do not withdraw from the study, they may choose at any time to have any portion of their data omitted, giving the dates and times between which they want their data to be removed.

Each consent form will be read and signed electronically, since this study is entirely on the web. Participants will indicate their consent to participate in this study by inputting their name and email to indicate that they have read and understood the informed consent document. Participants will be given the option to contact the research staff if they have any concerns regarding the consent. Participants will be emailed a copy of the consent form to their email address.

Finally, the study design includes an assurance of understanding quiz made up of 8 short questions about the study procedures. This includes questions on risks, benefits, data collection, data access and security, and privacy measures. Participants could only enroll in the study if they answered all 8 questions correctly.

Passive data collection begins only after participants have completed all onboarding surveys. To initiate passive data collection, participants must complete a comprehensive permission granting process in which they grant access to each data type in turn (eg, GPS signal and activity signal). The data will be collected in a manner that inherently restricts the granularity and detail of participant information. For example, data on app usage will be bundled by hourly bucket and by category of app rather than collecting individual app names and timestamps. As another example, location information is collected semantically (eg, “home,” “work,” or “other location”) rather than precisely (eg, GPS coordinates). That is, investigators do not know where participants geographically are; instead, they only possess information regarding whether participants spent time at certain semantic locations of interest.

Data will be encrypted from the point of collection to the point of delivery in the secure database and transmitted in this fashion. Even if these data were intercepted by a nefarious actor, they would be protected by ‎Secure Hash Algorithms 256 encryption and would only be accessible to systems that have the private decryption key (only the research team).

Data will be deidentified. Although this study is outside the bounds of HIPAA (Health Insurance Portability and Accountability Act; neither party is a covered entity or a business associate of a covered entity), the research team has removed all of the 18 HIPAA identifiers (name, email, address, etc) from the study data. The data will be stored in a secure, access-restricted, and password-protected database that is audited extensively at monthly, quarterly, semiannual, and annual intervals by security, privacy, and compliance teams and processes. Access to this database is restricted strictly to members of the research team who all completed Collaborative Institutional Training Initiative training.

There are two main types of data collected in the study: (1) study data, which include all active and passive investigational data (surveys, smartphone data, and wearable data) and (2) consent responses, which contain the participant consent forms. These 2 data sets are kept entirely separate. Consent forms must be retained for liability and legal purposes. Access to these forms is restricted to members of the research team who do not have access to the study data.

The institutional review board of the University of Oregon has approved the study protocol (STUDY00000162). In addition, this study went through several rounds of ethical reviews within Google, including sign-off from the responsible artificial intelligence team; the health ethics team; and the privacy, security, and legal teams. Further, an external advisory panel was assembled with mental health experts from outside of Google to solicit their input and feedback on the study design.

We leverage a raffle design for incentives and compensation. Participants who complete the required elements of the study will be eligible to enter the raffle to receive a US $50 gift card. Specifically, the conditions for eligibility were to (1) consent and enable sensor collection at study start, (2) complete the prestudy assessments, (3) complete a minimum cumulative of 7 days (1 week) of daily status assessments, and (4) complete the poststudy assessments. We will segment the raffles in batches of 1000 participants to avoid delaying delivery of the incentive until the completion of the study (which could be quite some time after the first several thousand participants complete the participant duration of 4 weeks). Up to 1610 participants may receive this incentive over the course of the study, with an 11.5% win ratio.

### Data Collection

#### Digital Measures

The study includes digital measurement from both smartphones and wearable physiological devices. After enrolling in the study, participants will be asked to grant permissions to their devices. Figure 2 shows screenshots of the phone app to illustrate the design.

**Figure 2 figure2:**
[figure not shown]
Screenshots of the Android phone app that will be used in the Digital Well-Being study. The app facilitates enrollment and consent, baseline and poststudy surveys, EMAs, and logging of the smartphone measures. Participants can optionally link their Fitbit account. EMA: ecological momentary assessment.

#### Mobile Data

Patterns of device use will be measured objectively via the study mobile app. The measurements will include:

Screen on time and app usage: the amount of screen time derived from smartphone app usage data such as time of day and day of week computed per app type—app usage will be quantified for categories of apps rather than individual apps and app categories will be determined by those listed on the Google Play Store.Mobility and semantic location information: various measures of geographic mobility will be discerned from GPS data such as daily count of travel or stop events per person per day; duration of each travel or stop event (minutes); and proportion of day spent at home, work, or some other location (labeled “other”).Human activity recognition from smartphone accelerometer: various movement patterns of human activities of interest such as stationary, walking, running, biking, and driving will be derived from data generated by smartphone accelerometers without being limited by phone location or orientation.Battery and charging status: smartphone battery status and plug-in or unplug events.

#### Wearable Data

We will collect the following data from participants who sign up with Fitbit devices. As access to devices can vary, participation is allowed with any generation of Fitbit devices. Different Fitbit devices have different sensors and algorithmic capabilities, and therefore not all the measures described below will be available for all participants. Minute-level features include accelerometer-based measures of steps and photoplethysmography-based heart rate measurements. Day-level features include accelerometer-based measures of activity (eg, total steps, number of floors climbed, and number of active zone minutes), sleep stages, duration and quality, minutely heart rate, daily resting heart rate, respiration rate during sleep, heart rate variability during sleep, skin temperature during sleep, blood oxygen saturation during sleep, and tonic electrodermal activity.

#### Survey Instruments

Participants will complete a battery of self-report questionnaires at the beginning (baseline) and end of the study (poststudy) as follows: (baseline only) demographics questionnaire and Big Five Inventory [21,22], Patient Health Questionnaire [21,23], Generalized Anxiety Disorder Scale [24], Patient-Reported Outcomes Measurement Information System Sleep Disturbance and Sleep-Related Impairment short form [25,26], Patient-Reported Outcomes Measurement Information System Emotional Support Short Form 4a [27,28], Shortened Smartphone Addiction Scale [29], and Perceived Stress Scale [27].

